### Follow-up assessment

Follow-up assessments take place at 12 weeks after randomisation and include an online questionnaire, physical activity monitoring and blood sample collection. Not all of the measures in the baseline questionnaire are repeated at follow up (Table 2). The follow-up questionnaire (available from the authors on request) should take no more than 20 min to complete. Participants are requested to complete this follow-up questionnaire and will receive two reminder emails at day 7 and day 14 after sending the follow-up questionnaire if it has not been completed. If we do not hear from participants by day 24, we will mark the data as missing.

**Table 2 Tab2:** INFORM measures at each stage of the study

	Measure or Instrument name	INTERVAL	INFORM baseline	INFORM follow-up	Mode of assessment	Note
Primary outcome	Physical Activity Level*	✓	✓	✓	accelerometers	using the Axivity AX3 – 3Axis logging Accelerometer®
Secondary outcomes	Traditional risk factors					
	Fruit and vegetables intake	✓		✓	carotenoids	
	Weight		✓	✓	self-report	as used in Godino et al. [56] and Knowles et al. [48]
	Cholesterol Panel (total, HDL and LDL cholesterol, triglycerides)	✓		✓	blood serum	
	Fructosamine	✓		✓	blood serum	
	Nutrition Behaviour (fruit, vegetables, whole grains, fish, red and processed meat)		✓	✓	self-report	one-item questions that reflect the present prevention guidelines on CVD [16, 10]
	Physical Activity Level		✓	✓	self-report	EPIC-Norfolk Physical Activity Questionnaire [60]
	Smoking Status		✓	✓	self-report	
	Alcohol Consumption		✓	✓	self-report	
	Current Medication and Healthcare Usage		✓	✓	self-report	adapted version of the Health Services Research Unit Aberdeen questionnaire [61]
	Perceived risk					
	Comparative and Absolute Cardiovascular Risk		✓	✓	self-report	adapted according to Diefenbach et al. [62] and used in other risk communication studies [48, 56]
	Cognitive evaluation of provision of coronary heart disease risk scores					
	Understanding of Risk Scores			✓	self-report	as used in another trial of risk communication [56]
	Perceived Accuracy of Risk Scores			✓	self-report	as used in other risk communication studies [48, 56]
	Acceptability of the Intervention			✓	self-report	in line with the Heart to Health study [50]
	Psychological outcomes					
	Stress		✓	✓	self-report	as used in the Randomized Trial of Personal Genomics for preventive cardiology [48]
	Mood		✓	✓	self-report	adapted from the Patient Health Questionnaire [63]

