	Coronary Heart Disease-related Worry		✓	✓	self-report	an adaptation of the Cancer Related Worry Scale [64]
	Genetic Risk-related Worry/Anxiety		✓		self-report	as used by Knowles et al. [48]
Moderators and mediators	Sociodemographic characteristics					
	Sex, Age, Ethnicity	✓			self-report	
	Marital Status		✓		self-report	
	Socioeconomic Status (level of education, level of income, living area)		✓		self-report	adapted from the European Health Interview Survey; deprivation level of the area based on the Index of Multiple Deprivation, Department for Communities and Local Government
	Numeracy Skills		✓		self-report	3-item Schwartz scale [65]
	Family History of Coronary Heart Disease		✓		self-report	
	History of Genetic Testing		✓		self-report	
	History of Coronary Heart Disease Risk Assessment		✓		self-report	
	Self-rated Health		✓	✓	self-report	Ware et al. [66]
	Barriers to risk-reducing strategy		✓		self-report	in line with the Heart to Health study [50]
	Cognitive and emotional theory-based antecedents to behaviour change					
	Intentions		✓		self-report	adapted according to Ajzen [67] and used in previous similar research [56]
	Perception of Diet		✓		self-report	
	Perception of Physical Activity		✓		self-report	
	Coronary heart disease risk Representations		✓		self-report	the Brief Illness Perceptions Questionnaire [68]
	Self-efficacy		✓		self-report	as used in previous behavioural research [56, 68]
	Response Efficacy		✓	✓	self-report	as used in previous behavioural research [52, 69]
	Social Support		✓		self-report	the Multidimensional Scale of Perceived Social Support [70]
	Time Orientation		✓		self-report	as used in a study by Peretti-Watel et al. [71]
	Sense of Coherence		✓		self-report	3-items scale, Lundberg et al. [72]
	Comparative Optimism		✓		self-report	comparative perceived risk

*participants who did not take part in physical activity monitoring during the INTERVAL Study will be required to undertake baseline activity monitoring over 7 days

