For each continuous secondary endpoint, the four pairwise differences will be estimated, together with 95 % confidence intervals, using ANCOVA as described for the primary outcome analyses (except Coronary Heart Disease-related Worry). The Coronary Heart Disease-related Worry will be measured only at follow-up, so the four pairwise differences will be estimated, together with 95 % confidence intervals, using linear regression. A 3 d.f. test will be performed of the null hypothesis that there is no difference between the four randomised groups. For categorical endpoints, similar analyses will be performed using logistic and multinomial regression models.

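### The analysis section and Table 2 disagree on whether Coronary Heart Disease-related Worry has a baseline, and the secondary outcomes that Table 2 does show at follow-up only have no analysis rule that fits them

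*Protocol article*

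**What the plan says.** The section Analysis design – randomised controlled trial sets a general rule: "For each continuous secondary endpoint, the four pairwise differences will be estimated", with 95% confidence intervals, "using ANCOVA as described for the primary outcome analyses (except Coronary Heart Disease-related Worry"). The primary-outcome model to which this refers takes the change between the two assessments as the response and the baseline value as a covariate. The single exception is then justified: "The Coronary Heart Disease-related Worry will be measured only at follow-up, so the four pairwise differences will be estimated" by linear regression. A 3 d.f. test across the four randomised groups follows, and categorical endpoints get similar analyses by logistic or multinomial regression. The Multiplicity section judges every secondary endpoint by the 3 d.f. test, at p<0.001.

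Table 2, in the section Follow-up assessment, is titled "INFORM measures at each stage of the study". Its row for "Coronary Heart Disease-related Worry", described as "an adaptation of the Cancer Related Worry Scale [64]", is ticked at INFORM baseline and at INFORM follow-up. The rows "Understanding of Risk Scores", "Perceived Accuracy of Risk Scores" and Acceptability of the Intervention are ticked at follow-up only. The Measures section lists understanding, accuracy and acceptability among the self-reported secondary outcomes, without giving their scale.

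Table 1, under Interventions, gives Group 1 nothing, Group 2 lifestyle advice only, Group 3 advice and a phenotypic score, and Group 4 advice and both scores. Whatever a group was not allocated is supplied when follow-up ends.

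**The concern.** The reason given for the one exception conflicts with the trial's own measurement schedule. A reader cannot tell whether the pre-specified model for Worry is a regression on follow-up values or a baseline-adjusted ANCOVA, so the choice stays open until after the data are seen. If the baseline was collected, the stated model also leaves out a covariate that would cost nothing to use.

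The exception also seems to be attached to the wrong outcome. The secondary outcomes that Table 2 does show without a baseline are the three evaluation items, and the general rule makes no allowance for them. For two of these, the quantity measured concerns a risk score that half the randomised groups have not been given when the 12-week questionnaire is completed.

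**Working it through.** The plan states no figure on this point, so there is none to reproduce. The check sets the statements side by side and then gives the scale of the precision loss.

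**1. Timing of each measure in Table 2, against the analysis rule**

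| Measure | INFORM baseline | INFORM follow-up | Rule in the analysis section |
|---|---|---|---|
| Stress | yes | yes | general rule |
| Mood | yes | yes | general rule |
| CHD-related Worry | yes | yes | exempted, as having no baseline |
| Understanding of Risk Scores | no | yes | general rule |
| Perceived Accuracy of Risk Scores | no | yes | general rule |
| Acceptability of the Intervention | no | yes | general rule |

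None of the six has an INTERVAL tick that could serve as a baseline. Worry has the same pattern as Stress and Mood, so a fault in reading the table is unlikely.

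**2. Can the general rule be applied to the evaluation items?** If they are continuous, the response is follow-up minus baseline and the covariate is baseline. With no baseline for anyone, neither exists. The missing-indicator method that the article plans for missing baseline data does not help: it handles a covariate missing for some participants, and cannot supply a change score when all baselines are absent. If they are categorical, the ANCOVA wording does not bind, but the four comparisons and the 3 d.f. test still do.

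**3. Which comparisons have an object at 12 weeks?** From Table 1:

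| Planned comparison | Understanding, Perceived Accuracy | Acceptability |
|---|---|---|
| 1: Group 1 vs 2 | neither group has a score | Group 1 has no intervention |
| 2: Group 3 vs 4 | meaningful | meaningful |
| 3: Groups 3+4 vs 1 | Group 1 has no score | Group 1 has no intervention |
| 4: Groups 3+4 vs 2 | Group 2 has no score | meaningful |
| 3 d.f. test, all four groups | includes Groups 1 and 2 | includes Group 1 |

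**4. Precision at stake for Worry, if its baseline exists.** With a within-group correlation r between baseline and follow-up, ANCOVA has residual variance (1 − r²) times that of the follow-up-only regression. Omitting the baseline therefore multiplies the standard error by 1/√(1 − r²). The article gives no r for Worry. Its 0.6, in the sample size section, is for accelerometer-measured activity, so r is varied here. The effective number is 186 × (1 − r²), using the 186 per group of the sample size calculation as a reference.

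| Assumed r | 1 − r² | Standard error multiplied by | Effective number out of 186 |
|---|---|---|---|
| 0.3 | 0.91 | 1.05 | 169 |
| 0.5 | 0.75 | 1.15 | 140 |
| 0.6 | 0.64 | 1.25 | 119 |
| 0.7 | 0.51 | 1.40 | 95 |

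**The case against.** **Table 2 may be the one in error.** If Worry was really asked only at follow-up, no baseline is discarded, no precision is lost and linear regression is the right model. The next row, Genetic Risk-related Worry/Anxiety, sits among the psychological outcomes yet is ticked at baseline only, which is odd for an outcome and weakens any presumption that these rows are correct. This stands. A reader might infer that a collected baseline is being thrown away; the article does not establish that, only that it contradicts itself.

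**The precision loss is doubly conditional.** It needs both a baseline and an assumed correlation, and at r = 0.3 it is only about 5%. The regression is also unbiased. Both points stand, which is why a range is given and no single figure is claimed.

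**Worry is not singled out as a harm outcome.** The Discussion mentions increased anxiety as a possible harm, so a reader might take Worry to be a main safety measure. The article does not say so: the Measures section's list of psychological outcomes does not name it, and it is one of many secondary measures.

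**The evaluation items may be categorical, and may be put only to some groups.** Their scale is not given, so it cannot be said outright that the plan applies ANCOVA to them. The questionnaire is not shown, and an unseen analysis plan may define who is analysed. Nor is Acceptability meaningless outside the score groups, since Group 2 receives lifestyle advice. These limits are accepted. What remains does not depend on missing detail: the article states a rule for each secondary endpoint with one named exception, and the four-group test in that rule cannot sensibly cover these items on either scale.

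**Conclusion.** The point holds as a contradiction that must be reconciled, with a related misfit in the same rule.

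- **Worry:** the analysis section and Table 2 cannot both be right, and the difference decides the model. Confidence in the mismatch is high. Which statement is wrong cannot be told from the article. The consequence is an ambiguous pre-specification and, if the baseline exists, the range of precision loss shown above. There is no bias.
- **Evaluation items:** Understanding, Perceived Accuracy and Acceptability have no baseline and no exemption. Change-from-baseline ANCOVA is impossible for any that are continuous. The four-group 3 d.f. test lacks an object in Groups 1 and 2 for the first two items, and in Group 1 for Acceptability. This rests on Table 1 and on omitted information being given only after follow-up ends.

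The primary outcome, the key secondary outcome (carotenoids) and the sample size are untouched. The correction should be made, but it does not threaten the trial's main conclusions.

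**What to change.** 1. Check the baseline questionnaire for the Worry items. If they were asked, delete the exception and analyse Worry by the same baseline-adjusted ANCOVA as the other continuous endpoints. If they were not, correct Table 2 and keep the linear regression. Settle this before outcome data are examined by group.
2. Give the follow-up-only items their own sentence: no baseline term and no four-group 3 d.f. test. Compare Group 3 with Group 4 for Understanding and Perceived Accuracy of Risk Scores, and analyse Acceptability of the Intervention among Groups 2 to 4. Use linear, logistic or multinomial regression according to the scale, which should be stated.
3. Amend the Multiplicity section so that its 3 d.f. criterion is not applied to these three items.

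The cost is wording in the protocol and analysis plan. No new data, visits or participants are needed.

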### Measures

Table 2 provides details of the measures collected in the INFORM study and the stage of the study at which each is assessed. The primary outcome is objectively measured physical activity, defined as average acceleration (m/s^2^) over the observation period. Participants are instructed to continuously wear the accelerometer for 7 consecutive days and nights, and to carry on with all normal activities during this time. The accelerometers are waterproof and can be worn while swimming and showering. Accelerometers have been chosen as a measure of physical activity because they cause low participant burden and are not subject to the reporting bias or recall problems associated with the self-report methods [52].

The key secondary outcome, dietary behaviour, is objectively measured by levels of six serum carotenoids (alpha-carotene, beta-carotene, lutein, lycopene, beta-cryptoxanthin, zeaxanthin). Carotenoids are biologically active pigments in plants but are not synthesised in animals and as such they represent a valid biomarker of vegetable and fruit intake [53].

Other objectively measured secondary outcomes include total, HDL and LDL cholesterol and fructosamine. We also collect self-reported secondary outcomes via an online questionnaire. They include cardiovascular risk factors (self-reported weight, smoking status, alcohol consumption, physical activity and dietary behaviour); current medication and healthcare usage; perceived risk (perception of comparative and absolute risk); cognitive evaluation of provision of CHD risk scores (understanding, accuracy, acceptability); and psychological outcomes (anxiety associated with testing, fatalism, depression, stress and mood).

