#### Analysis design – randomised controlled trial

All trial analyses will be based on the Intention To Treat (ITT) principle. Those with missing follow-up data will be excluded from the analyses (a complete case approach). We will perform sensitivity analyses to assess the impact of missing follow-up data on the results. Participants with missing baseline data will be included in the analyses using the missing-indicator method [59].

The null hypothesis for the primary analysis is that there is no difference between any of Groups 1 to 4. Estimates of the following pairwise differences will be calculated: 1) Group 1 (control group) vs. Group 2 (lifestyle advice only) – to estimate the effect of providing lifestyle advice compared with no intervention; 2) Group 3 (phenotypic risk score and lifestyle advice) vs. Group 4 (phenotypic and genetic risk scores and lifestyle advice) – to estimate the effect of providing a genetic risk score in addition to lifestyle advice and a phenotypic risk score; 3) Group 3 + Group 4 vs. Group 1 – to estimate the effect of providing risk score information and lifestyle advice compared with no intervention, and 4) Group 3 + Group 4 vs. Group 2 – to estimate the effect of providing risk score information in addition to lifestyle advice.

Mean changes in objectively measured physical activity between baseline and 3-month follow-up will be analysed using analysis of covariance (ANCOVA). The ANCOVA model will model change (follow-up minus baseline) in objectively measured physical activity, adjusted for baseline. A test involving three degrees of freedom (3 d.f.) will be performed of the null hypothesis that there is no difference between the four randomised groups. If the p-value from this test is <0.01, this will imply that there are differences between the groups. The ANCOVA model will also be used to derive estimates of the differences in mean change and 95 % confidence intervals for each of the four pairwise comparisons described above. To avoid detracting the focus of the results from the overall 3 d.f. test, *p*-values for each of the pairwise comparisons will not be calculated.

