#### Multiplicity

Given the number of endpoints, randomised groups and therefore comparisons, the results for the primary endpoint will be regarded as convincing if the *p*-value from the 3 d.f. test is <0.01, while the results for each secondary endpoint will be regarded as convincing if the relevant *p*-value from the 3 d.f. test is <0.001.

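### Secondary endpoints with more than two categories go to multinomial regression, which does not produce the 3 d.f. test that the decision rule names and ignores any ordering of the answers

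*Protocol article*

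**What the plan says.** Under Analysis design – randomised controlled trial, continuous secondary endpoints get four pairwise differences with 95% confidence intervals, and an overall test: "A 3 d.f. test will be performed of the null hypothesis that there is no difference between the four randomised groups". For the rest, the section says: "For categorical endpoints, similar analyses will be performed using logistic and multinomial regression models". No ordinal model is named.

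Under Multiplicity, one rule covers all secondary endpoints, continuous or categorical: "the results for each secondary endpoint will be regarded as convincing if the relevant *p*-value from the 3 d.f. test is <0.001".

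The Measures section and Table 2 list self-reported secondary outcomes that are graded by nature. They include comparative and absolute perceived risk, and diet items described as "one-item questions that reflect the present prevention guidelines on CVD". The article does not state the response scales, the number of levels, or which items will be analysed as categorical.

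**The concern.** Two fixed parts of the plan do not fit together. The analysis section chooses the model, and the Multiplicity section chooses the test and threshold that decide whether a result is convincing. By naming multinomial as well as logistic regression, the plan itself expects some endpoints with more than two levels. For those, the standard overall group test does not have 3 d.f., and each planned contrast becomes K−1 odds ratios instead of one effect with one interval.

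There is a second, conditional cost. A multinomial model treats the levels as unordered labels. If the endpoint is ordered and the intervention moves answers consistently along the scale, that movement is spread over 6 to 12 d.f. and then judged at a strict 0.001. A real effect on perceived risk or a diet item is then easier to miss.

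**Working it through.** **Inputs from the protocol article.** Four randomised groups; secondary threshold 0.001; 186 evaluable participants per group (Sample size calculation). The article's own totals reproduce: 186 / (1 − 0.20) = 232.5, rounded up to 233, and 4 × 233 = 932. It gives no power calculation for any categorical secondary endpoint.

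**Inputs that are assumptions.** K levels, equally likely in Groups 1 and 2; a proportional-odds shift with odds ratio (OR) 2.0 in Groups 3 and 4; no baseline adjustment. The article gives none of these.

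**Step 1: degrees of freedom.** A multinomial model has K−1 equations, each with 4−1 group coefficients, so the global test has 3(K−1) d.f. A proportional-odds model has one set of three group coefficients, so its test has 3 d.f. for any K.

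| K | Multinomial d.f. | Critical value at 0.001 | Odds ratios per contrast |
|---|---|---|---|
| 2 | 3 | 16.27 | 1 |
| 3 | 6 | 22.46 | 2 |
| 4 | 9 | 27.88 | 3 |
| 5 | 12 | 32.91 | 4 |

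This step needs no assumption about scales or effects.

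**Step 2: power for an ordered endpoint with a consistent shift.** The likelihood-ratio noncentrality is λ = 2n Σ p·ln(p / p̄), summed over groups and levels, with p̄ the mean over groups and n = 186. Power is P(noncentral χ² with parameter λ > critical value).

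Worked case, K = 3. Groups 1 and 2 have probabilities (1/3, 1/3, 1/3). Halving the cumulative odds gives (0.2, 0.3, 0.5) in Groups 3 and 4. The mean is (0.267, 0.317, 0.417). The sum is 0.0171 for each reference group and 0.0174 for each shifted group, so λ = 2 × 186 × 2 × (0.0171 + 0.0174) ≈ 25.67. On 6 d.f. the power is 80.0%; on 3 d.f. it is 89.5%.

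| K | λ | Multinomial | Ordinal, 3 d.f. | Difference (points) |
|---|---|---|---|---|
| 2 | 21.37 | 79.5% | 79.5% | 0 |
| 3 | 25.67 | 80.0% | 89.5% | 9.5 |
| 4 | 27.20 | 75.9% | 92.0% | 16.1 |
| 5 | 27.92 | 70.9% | 92.9% | 22.0 |

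Simulation of 400 trials per setting agreed: 79.5% v 88.8% for K = 3, and 73.5% v 93.8% for K = 5.

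**Step 3: how far the size depends on the assumptions.** With K = 5 and the same pattern, OR 1.5 gives 9.0% v 26.3% and OR 2.5 gives 98.0% v 99.9%. If Groups 2 to 4 all shift by OR 2.0, K = 5 gives 46.9% v 78.4%. Across K = 3 to 5, OR 1.5 to 2.5 and three effect patterns, the loss runs from under 1 point to about 31 points.

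**Step 4: a case that goes the other way.** Let Groups 1 and 2 answer 30/40/30% and Groups 3 and 4 answer 40/20/40%. Then λ = 35.95 and the 6 d.f. multinomial test has about 96% power. A proportional-odds test has almost none, because the change is symmetric and the common odds ratio is 1.

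**The case against.** **The article never says that an ordered item goes to the multinomial model.** This stands. Response scales are in questionnaires that are not shown, coding can be left to an analysis plan, and the one self-report scale whose model is named individually, CHD-related worry, is treated as continuous. Other ratings might be scored the same way. The power argument therefore applies only to ordered items that are analysed as categorical.

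**Logistic regression could be read to include ordinal logistic regression.** The wording does not exclude it, but binary logistic beside multinomial is the natural reading. The d.f. mismatch remains for any endpoint that does go to the multinomial model.

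**The multinomial model may suit this trial.** The Background allows for motivation or a defeatist response, and the Discussion for anxiety or false reassurance. Effects in both directions can break proportional odds, as Step 4 shows. This stands, and is why the assumption needs checking and the multinomial fit should be kept alongside.

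**Stronger readings that the article does not support.** A reader might infer that the plan's false-positive rate exceeds 0.001. That would need an analyst to compare a 6 to 12 d.f. statistic with the 3 d.f. critical value, and nothing in the plan directs this. Referred to its own d.f., the multinomial test holds its level. A reader might also count understanding and perceived accuracy of the risk scores among the affected ordered endpoints. Table 2 measures both only at follow-up, and Groups 1 and 2 have received no risk score by then, so a four-group comparison of them is not meaningful and the power figures do not apply.

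**Conclusion.** The mismatch is exact: for any categorical endpoint with more than two levels, the named model gives a 3(K−1) d.f. test, while the decision rule asks for 3 d.f. Because the article fixes both parts, this is a stated inconsistency rather than a detail left for later.

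The loss of power is real but conditional. It needs an ordered endpoint analysed as categorical and an effect that is roughly a consistent shift. Under the stated assumptions it is about 10 to 22 points for three to five levels at OR 2.0 in Groups 3 and 4. It would be wrong to conclude that the plan loses power on categorical endpoints in general: binary endpoints lose nothing, unordered ones belong in the multinomial model, and non-monotone effects can reverse the comparison. The primary endpoint, its sample size and the carotenoid outcome are untouched. The point should be corrected before analysis, but it does not threaten the trial's main conclusion.

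**What to change.** In Analysis design – randomised controlled trial, replace the sentence on categorical endpoints with text such as: *Binary endpoints will be analysed by logistic regression. Ordered categorical endpoints will be analysed by proportional-odds logistic regression, adjusted for baseline where measured, with a 3 d.f. test of the four groups and one odds ratio with 95% confidence interval per contrast. The proportional-odds assumption will be checked, and the multinomial fit reported as a sensitivity analysis. Unordered endpoints with K levels will be analysed by multinomial regression with a 3(K−1) d.f. test.*

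In Multiplicity, apply the 0.001 threshold for secondary endpoints to *the global test of the four groups*, whatever its d.f.

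This changes wording only and needs no new data. The price is that the common odds ratio rests on proportional odds and can hide movement in both directions; the check and the sensitivity analysis are there to show it.
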